### Randomization and blinding

Eligible participants will be randomly assigned to either the intervention group (Tuina + rTMS) or the control group (CBT) in a 1:1 ratio. A computer-generated randomization sequence will be prepared using the “proc plan” procedure in SAS 9.4 (SAS Institute Inc.), employing randomly permuted block sizes to ensure balanced group allocation. An independent researcher, uninvolved in recruitment, intervention, or data analysis, will generate the sequence. Each allocation will be concealed in a sequentially numbered, opaque, sealed envelope, securely stored to maintain allocation concealment. At the point of enrollment, the recruiting investigator will open the next envelope in sequence to determine group assignment. To minimize bias, outcome assessors, and statisticians will remain blinded to group allocation throughout the trial. Given the nature of the intervention, it is not feasible to blind PSD participants or treatment providers to group allocation. All participants will receive the same standard information about the study objectives and procedures at baseline without disclosing specific group assignments. Furthermore, both groups will receive interventions with identical frequency, duration, and therapist interaction time to control for nonspecific therapeutic effects. Statisticians, administrators, data collectors, and outcome assessors will be blinded during the study. And blinding will only be broken after data analysis is completed.

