### Intervention group

#### Tuina procedure

Tuina will be performed by an experienced, licensed therapists, who has more than 5 years of experience in clinical massage therapy. Participants lie in a prone or lateral position on therapy bed. The acupoints along the Governor Vessel (GV) are located, including Baihui (GV20), Dazhui (GV14), Zhiyang (GV9), Mingmen (GV4), and Changqiang (GV1). An ointment (1–3 g) is evenly applied to each acupoint. This ointment contains no active pharmacological ingredients and is used solely as a lubricant to facilitate manual techniques. The therapist applies thumb pressure and kneading techniques to each acupoint for 2 min. Subsequently, a three-finger massaging technique (index, middle, and ring fingers) is performed along the line connecting Dazhui (GV14) to Changqiang (GV1) for 10 min. Finally, palm-rubbing is used along the spine of the Governor Vessel from top to bottom for 30 s. Prior to treatment, therapists undergo 1 week of training using a TN-II massage technique measurement device. This ensures consistent application pressure of 0.5 kg and a frequency of 100 ± 10 strokes per minute during the procedures. Tuina therapy is conducted five times per week over 2 weeks, with each session lasting approximately 20 min.

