#### rTMS intervention procedure

Patients are positioned comfortably in a seated or semi-reclined position on a therapy chair specifically designed for TMS treatment. The head is stabilized to minimize movement during the intervention. A figure-eight-shaped coil is used, placed tangentially to the scalp over the left dorsolateral prefrontal cortex (DLPFC), which has been identified as a key region associated with depression.

The stimulation parameters are set as follows:

*Frequency*: High-frequency stimulation (10 Hz) is commonly employed for left DLPFC.*Intensity*: The intensity is typically set at 80% of the motor threshold (MT), individualized based on the patient’s resting MT, which is identified by observing the minimal intensity required to elicit a motor response in the contralateral abductor pollicis brevis muscle.*Pulse train*: A single train consists of 20 pulses/sequences of stimulation followed by a 20-s rest period.*Total pulses*: 60 sequences, 1,200 pulses per session.*Frequency of sessions*: rTMS is administered once daily, five times per week, over a total of 2 weeks.

To ensure consistency and safety, all rTMS sessions are performed by certified clinicians under strict adherence to standardized protocols. Adverse events, such as mild headache or scalp discomfort, are closely monitored and documented during and after each session.

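### The arms are said to be identical in duration and therapist contact, but the stated schedules match only in session frequency and course length

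*Protocol article*

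**What the plan says.** Under Randomization and blinding, the protocol article accepts that "it is not feasible to blind PSD participants or treatment providers to group allocation". It then says that "both groups will receive interventions with identical frequency, duration, and therapist interaction time to control for nonspecific therapeutic effects". The limitations paragraph of the Discussion returns to this. It concedes that double-blinding is difficult and may leave bias, and answers with blinded assessors and analysts together with equal therapist contact and matched frequency and duration in the two arms.

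The intervention sections give these schedules:

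- **Tuina:** "Tuina therapy is conducted five times per week over 2 weeks, with each session lasting approximately 20 min".
- **rTMS:** "rTMS is administered once daily, five times per week, over a total of 2 weeks". The parameters are "High-frequency stimulation (10 Hz) is commonly employed for left DLPFC", "A single train consists of 20 pulses/sequences of stimulation followed by a 20-s rest period" and "60 sequences, 1,200 pulses per session". No session length in minutes is given.
- **CBT (Control group section):** sessions of about 30 min, five per week for 2 weeks, preceded at baseline by a 3-hour educational seminar held in a group. The seminar is described as part of the CBT training and appears nowhere in the intervention arm's description.

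**The concern.** Patients and therapists know the allocation, and the arms differ completely in kind: manual therapy and a device on one side, talking therapy on the other. Blinded rating of the HAMD-17 protects against a biased assessor. It does not remove the effect that attention, time and expectation may have on the patient's own mood. Matched contact is the feature that the protocol names as the control for such effects, so a reader will rely on it when interpreting a between-arm difference. If the schedules do not show that matching, the article credits the design with a safeguard that it does not have as described.

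**Working it through.** **Inputs**

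- Tuina: about 20 min per session, ten sessions (Tuina procedure).
- rTMS: 10 Hz, 20 pulses per train, 20 s rest after each train, 60 trains, ten sessions (rTMS intervention procedure).
- CBT: about 30 min per session, ten sessions, plus one 3-hour group seminar (Control group).

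**Reproducing the stated figures**

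- rTMS pulses: 60 × 20 = 1,200, as stated.
- Tuina components: 5 acupoints × 2 min + 10 min + 0.5 min = 20.5 min, consistent with the stated figure of about 20 min.

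**rTMS session length**

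- One train: 20 pulses / 10 Hz = 2 s.
- One session: 60 × (2 + 20) s = 1,320 s = 22 min, or 21.7 min if the last rest is not counted.
- This covers pulses and rests only. Positioning, head stabilisation, coil placement and motor-threshold determination come on top.

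**Comparison of the arms**

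| Quantity | Tuina + rTMS | CBT | Same? |
|---|---|---|---|
| Sessions of each treatment per week | 5 | 5 | yes |
| Course length | 2 weeks | 2 weeks | yes |
| Scheduled time per treatment day | 20 + 22 = 42 min | 30 min | no (42/30 = 1.40) |
| Scheduled time per week | 5 × 42 = 210 min | 5 × 30 = 150 min | no |
| Scheduled time over the course, seminar excluded | 10 × 42 = 420 min | 10 × 30 = 300 min | no |
| Baseline seminar | none described | 180 min, in a group | no |
| Clock time including the seminar | 420 min | 300 + 180 = 480 min | no |
| Therapist contact during rTMS | not stated | not applicable | cannot be checked |

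The daily figure assumes that Tuina and rTMS fall on the same five days. The weekly and course totals do not depend on that. With the Tuina components summed (20.5 min) and the last rest kept or dropped, the daily total stays between 41.7 and 42.5 min.

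The difference changes sign. The intervention arm has 12 min more per treatment day, while the CBT arm has 480 − 420 = 60 min more clock time over the whole course once the seminar is counted.

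The uniform baseline information mentioned under Randomization and blinding concerns the study's aims and procedures. Nothing there says that the intervention arm attends the seminar.

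**The case against.** **Duration may mean the 2-week course.** On that reading the word is correct, and this stands. But therapist interaction time is a separate item in the same sentence. It gains no support from equal course length when one arm alone has a 180-min seminar.

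**Scheduled minutes are not contact minutes.** This also stands, and it rules out the stronger reading. A reader might infer from 42 against 30 min that the intervention arm gets more therapist contact. Counting hands-on Tuina alone (about 20 min), a reader might equally infer that it gets less. The documents support neither. Of the 22 rTMS minutes, 2 are pulse delivery (60 × 2 s) and 20 are rests, and the article does not say how much of this the clinician spends with the patient. Nor is 22 min an upper limit, because set-up and threshold determination are extra and "Adverse events, such as mild headache or scalp discomfort, are closely monitored and documented during and after each session". Equality cannot be excluded. If, as an assumption, 10 min of each rTMS session were contact, session contact would be 20 + 10 = 30 min in both arms, although the seminar would still be unmatched. If 28 min were contact, set-up included, the course total would be 10 × (20 + 28) = 480 min, the same as CBT with every seminar minute counted.

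**This is a condensed article, and the full protocol may record contact minutes.** Their absence is therefore not held against the article. The point rests on an affirmative claim of identity set beside schedules printed in the same article.

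**The stated lengths are approximate.** Rounding does not explain a gap of 12 min on 30, or a 3-hour component in one arm.

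**The Discussion is already cautious.** It lists the lack of double-blinding as a limitation and says only that the measures are meant to help. The blinding of assessors and statisticians is untouched, and the schedules are openly stated. This limits the harm, but equal contact is still offered as part of the remedy.

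**Conclusion.** The claim of identical duration and therapist contact is wrong as written. What is matched is session frequency and course length. Scheduled session time differs by about 12 min per treatment day (about 42 against 30 min, 40% more) and by about 120 min over ten treatment days (420 against 300 min). The 180-min group seminar belongs to the CBT arm only.

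The 22 min for rTMS is derived from the pulse parameters, takes 10 Hz as the frequency actually used, and excludes set-up. The two mismatches in scheduled time and seminar follow from the stated figures. Equal therapist contact is a different matter: it is unproven, not disproved.

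A reader might also infer that the HAMD-17 comparison is biased towards one arm. The documents do not support that. The time imbalance reverses once the seminar is counted, and nothing in the article says how a minute of group teaching, massage or coil time compares with a minute of CBT. The consequence is an overstated claim of internal validity, with direction and size of any bias unknown. It should be corrected because it affects what a between-arm difference can be taken to mean.

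**What to change.** 1. In Randomization and blinding and in the limitations paragraph of the Discussion, replace the statements on identical or matched duration and equal therapist contact with a statement that the arms have the same session frequency and course length. Remove the statement that this controls for nonspecific effects.
2. Add to the limitations that scheduled session time differs (about 42 against 30 min per treatment day, rTMS set-up excluded) and that only the CBT arm attends the 3-hour group seminar.
3. State that any HAMD-17 difference will be read as the Tuina plus rTMS package against the CBT package including the seminar.
4. Optionally, record session minutes on the case report form and report them by arm.

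The cost is a text change in two places, one added limitation, one sentence on interpretation and, if wanted, one form field. Sample size and analysis stay as they are. The downside is a weaker internal-validity claim.

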### Intervention

During the two-week study period, standard stroke treatments such as antiplatelet agents, antihypertensive drugs, antidiabetic medications, and lipid-lowering drugs will be permitted. The use of these medications will be meticulously documented for each participant.

### Intervention group

#### Tuina procedure

Tuina will be performed by an experienced, licensed therapists, who has more than 5 years of experience in clinical massage therapy. Participants lie in a prone or lateral position on therapy bed. The acupoints along the Governor Vessel (GV) are located, including Baihui (GV20), Dazhui (GV14), Zhiyang (GV9), Mingmen (GV4), and Changqiang (GV1). An ointment (1–3 g) is evenly applied to each acupoint. This ointment contains no active pharmacological ingredients and is used solely as a lubricant to facilitate manual techniques. The therapist applies thumb pressure and kneading techniques to each acupoint for 2 min. Subsequently, a three-finger massaging technique (index, middle, and ring fingers) is performed along the line connecting Dazhui (GV14) to Changqiang (GV1) for 10 min. Finally, palm-rubbing is used along the spine of the Governor Vessel from top to bottom for 30 s. Prior to treatment, therapists undergo 1 week of training using a TN-II massage technique measurement device. This ensures consistent application pressure of 0.5 kg and a frequency of 100 ± 10 strokes per minute during the procedures. Tuina therapy is conducted five times per week over 2 weeks, with each session lasting approximately 20 min.

#### rTMS intervention procedure

Patients are positioned comfortably in a seated or semi-reclined position on a therapy chair specifically designed for TMS treatment. The head is stabilized to minimize movement during the intervention. A figure-eight-shaped coil is used, placed tangentially to the scalp over the left dorsolateral prefrontal cortex (DLPFC), which has been identified as a key region associated with depression.

The stimulation parameters are set as follows:

*Frequency*: High-frequency stimulation (10 Hz) is commonly employed for left DLPFC.*Intensity*: The intensity is typically set at 80% of the motor threshold (MT), individualized based on the patient’s resting MT, which is identified by observing the minimal intensity required to elicit a motor response in the contralateral abductor pollicis brevis muscle.*Pulse train*: A single train consists of 20 pulses/sequences of stimulation followed by a 20-s rest period.*Total pulses*: 60 sequences, 1,200 pulses per session.*Frequency of sessions*: rTMS is administered once daily, five times per week, over a total of 2 weeks.

To ensure consistency and safety, all rTMS sessions are performed by certified clinicians under strict adherence to standardized protocols. Adverse events, such as mild headache or scalp discomfort, are closely monitored and documented during and after each session.

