**Figure 1 fig1:**
[figure not shown]
Participant flow chart.

**Table 1 tab1:** Study schedule.

Study procedure	Period				
Time point	−1 week	0 week	2 week	6 week	14 week
Entry and administrative					
Eligibility screen	X				
Demographics	X				
Medical history	X				
Informed consent	X				
Randomization	X				
Interventions					
Tuina+rTMS		X	X		
CBT		X	X		
Outcome measures					
HAMD-17		X	X	X	X
fMRI		X	X		
NIHSS		X	X	X	X
MBI		X	X	X	X
MMSE		X	X	X	X
fNIRS		X	X		
Blood parameters		X	X		
Safety evaluations		X	X	X	X
Drug combinations		X	X	X	X
Patient compliance		X	X	X	X
Adverse events		X	X	X	X

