### Control group

Cognitive behavioral therapy is a widely recognized non-pharmacological intervention for PSD, focusing on modifying negative thought patterns and maladaptive behaviors that contribute to emotional emotional distress and impaired functioning. CBT training consists of a 3-h group-based health education seminar delivered at baseline to provide psychoeducation on stroke and emotional well-being, followed by a 2-week structured course comprising five sessions per week. Each CBT session lasts approximately 30 min and is conducted under the supervision of a qualified therapist with over 5 years of professional experience in psychotherapy. Interventions include:

Disease education: Introduce the causes, clinical manifestations, and treatment methods of PSD formation to patients, enabling them to gain a basic understanding of the disease and guiding them to actively cooperate with treatment.Establishing trust: Proactively caring for patients, harmonizing doctor-patient relationships, enhancing doctor-patient trust, creating a warm, relaxed, and confident emotional environment for patients, and enhancing their sense of security.Identifying negative emotions: comprehensively understanding the patient’s emotions, mentality, exploring their negative factors and automatic thoughts.Changing Negative Cognition: Actively Identifying and Improving Potential Functional Impairment.

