### Participant safety

When patients involved in this study, they will be required to understand the whole research plan, and sign the informed consent. In order to better prevention and treatment in this study may cause any damage, the researchers will detect any potential adverse events and truthfully recorded on the CRF table. In this study, adverse events is mainly related to treatment, including dizziness, headache, shortness of breath, palpitation. In the event of adverse events, will be in accordance with the contingency plans for processing. The investigator will first determine the severity of the adverse effects. Slight ae will by the doctor to treat. Serious ae report to the ethics committee will be made by the researchers.

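### Session-by-session adverse-event recording is written for rTMS but not for the equally frequent CBT sessions, so arm-level counts of non-specific events may not be comparable

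*Protocol article*

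**What the plan says.** Four places in the protocol article bear on how adverse events are collected.

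- **rTMS intervention procedure.** The schedule is "rTMS is administered once daily, five times per week, over a total of 2 weeks", and the safety instruction is "Adverse events, such as mild headache or scalp discomfort, are closely monitored and documented during and after each session".
- **Control group.** After a baseline seminar, CBT is "followed by a 2-week structured course comprising five sessions per week". On delivery the section says: "Each CBT session lasts approximately 30 min and is conducted under the supervision of a qualified therapist". It does not mention adverse events. The Tuina procedure does not either.
- **Table 1, Study schedule.** There is one row for adverse events and one for safety evaluations, each marked at weeks 0, 2, 6 and 14 and not split by arm.
- **Participant safety.** This section covers all participants: "the researchers will detect any potential adverse events and truthfully recorded on the CRF table". It gives no timing or method of elicitation. It describes the expected events as follows: "adverse events is mainly related to treatment, including dizziness, headache, shortness of breath, palpitation".

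Randomization and blinding adds that neither participants nor treatment providers can be blinded, and that the two arms are matched on treatment frequency and therapist contact.

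**The concern.** How many mild events a trial records depends heavily on how often patients are asked. Headache and dizziness are common in stroke survivors whatever their treatment. If one arm is checked around every session and the other under an unspecified routine, the first will tend to show more events even when the true rates are equal.

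The article does not simply leave elicitation to a fuller document. It states an intensive method and attaches it to one component of one arm. A team following the text as written would have a session-level instruction for rTMS and none for CBT. The article does not say who makes the rTMS session record. If it is the treating staff, they know the allocation, and blinding of outcome assessors does not protect that record.

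Safety is part of the case made for the trial: the Introduction looks for safer options than drug treatment. Arm-level adverse-event counts are likely to be reported and read side by side. A detection excess would count against Tuina plus rTMS, and under-recording in CBT would flatter the control. Mild events that go unrecorded in the CBT arm cannot be reliably recovered afterwards.

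**Working it through.** **The plan's own figures.** The article gives no adverse-event rate and no safety power figure. Its one calculation is the sample size, which supplies the arm size used below:

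- n = (1.96 + 0.84)² × 2 × 4.49² / 2.5² = 50.58, rounded up to 51 per group.
- With 20% dropout, 51 / (1 − 0.20) = 63.75, rounded up to 64 per group.

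Both match the article, and this point does not affect them.

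**Stated collection, side by side.**

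| | Tuina + rTMS | CBT |
|---|---|---|
| Treatment sessions | 5 × 2 = 10 (rTMS) | 5 × 2 = 10 |
| Sessions with a stated adverse-event check | 10 | 0 |
| Dated collection in Table 1 | weeks 0, 2, 6, 14 | weeks 0, 2, 6, 14 |
| General duty to detect any event | yes, untimed | yes, untimed |

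The contact opportunities are equal and the last two rows are identical. The arms differ only in the stated session-level check.

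**What unequal capture could do.** The inputs here are assumptions, because the documents give none. In both illustrations the true risk is the same in the two arms.

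*Illustration A: risk per patient.* True risk p is 10% to 30%. Capture is complete in the rTMS arm and a fraction s in the CBT arm. The spurious difference is p × (1 − s), and the spurious risk ratio is 1/s. The last column is the chance of a nominally significant difference (two-sided 5%, 64 per arm).

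| s | Risk ratio | Difference, p = 10% / 20% / 30% | Chance of p < 0.05 |
|---|---|---|---|
| 100% | 1.00 | 0 / 0 / 0 points | 5% |
| 75% | 1.33 | 2.5 / 5 / 7.5 points | 7% / 11% / 16% |
| 50% | 2.00 | 5 / 10 / 15 points | 19% / 35% / 53% |

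*Illustration B: risk per session.* The true risk is 5% per session over 10 sessions.

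- Complete capture: 1 − 0.95¹⁰ = 40.1% of patients with at least one recorded event.
- 75% of episodes captured: 1 − (1 − 0.0375)¹⁰ = 31.8%, a gap of 8.4 points.
- 50% of episodes captured: 1 − (1 − 0.025)¹⁰ = 22.4%, a gap of 17.8 points.

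These figures show direction and rough scale. They are not bounds, since other assumed rates would give other gaps.

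**The case against.** The strongest reply is that the article nowhere restricts adverse-event recording in the CBT arm. The Control group section describes the content of therapy and is silent on safety. The safety section applies to everyone, asks for any potential event to be detected, and sets no limit by arm or visit. Control patients are seen just as often. Table 1 also marks the interventions only at weeks 0 and 2 although they are given five times a week, so its columns cannot be read as listing every contact. Closer observation of a device procedure is ordinary practice, and the form and timing of elicitation may well be set in the full protocol. Finally, no between-arm test of adverse events is described, and safety is neither a primary nor a secondary outcome.

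Most of this stands, and it rules out several stronger readings that a reader might infer:

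- *Events are sought only at scheduled visits under CBT.* That would be an inference from silence; no section says it. A ratio of checks such as 11 to 1 depends on it and is not supported.
- *The two sets of named events conflict.* They do not. Both are open-ended examples, headache is in both, and one is specific to rTMS while the other is trial-wide. They are not separate lists for the two arms.
- *Recording is limited to events judged treatment-related.* That phrase describes what is expected; the same section asks for any potential event.
- *Safety rates will not be comparable.* The text supports only that they may not be.

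The reply does not remove the asymmetry that the article does state. An untimed general duty does not turn a session-level instruction for one arm into the same procedure for both. The lack of a formal test does not help either, because descriptive counts by arm would carry the same bias.

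**Conclusion.** The point holds as a modest and inexpensive improvement. As written, adverse events are to be documented around each of 10 rTMS sessions, with no matching instruction for the 10 CBT sessions. The remaining collection is common to both arms and does not equalise this. Arm-level counts of non-specific events may therefore not be comparable, and the likely direction is an excess in the intervention arm from detection alone.

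The size cannot be derived from the documents. It is zero if CBT events are captured equally well. If CBT captured half, it would be up to about 15 points (true risk per patient up to 30%) or about 18 points (true risk 5% per session). All these rates and capture fractions are assumptions. The sample size and the efficacy outcomes are untouched. If the full protocol already sets common elicitation, one sentence saying so settles the matter.

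**What to change.** State one adverse-event procedure for both arms:

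- Use the same short form, including an open question, at each of the 10 treatment sessions in both arms and again at weeks 2, 6 and 14.
- State in the text that events are recorded whatever their presumed relation to treatment, in line with the general duty already given.
- Base any between-arm safety summary on this common collection only.
- Report local rTMS effects such as scalp discomfort separately, since they have no counterpart under CBT.

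Patients already attend these sessions, so the cost is one form and a few minutes of extra recording per CBT session. Monitoring during rTMS sessions stays as it is.
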